### **3.5 Study groups**

#### **3.5.1 Intervention Group**

The Intervention Group will be represented by hospitalized adult clinical patients who have the definition of difficult venous access (DIVA) *Difficult Intravenous Access*, characterized by the occurrence of two or more failed attempts at peripheral venous access using traditional technique, with no visible and palpable veins or a patient with a declared or documented history of difficult venous access and medical indication for continuous or intermittent intravenous therapy for more than five and a maximum of 30 days of treatment. These patients will receive an ultrasound-guided (US) 18G (8 or 10 cm), 20G (8 or 10 cm), 22G (8 or 8 cm) PowerGlide Pro™ Midline catheter. The insertion will be performed by the Nurses of the Vascular Access Program of HCPA – PICC Adult Team, all with more than five years of experience in ultrasound-guided venipuncture, with previous theoretical-practical training for catheter insertion and maintenance. The insertions will be at the bedside, with adherence to standard sterile barrier precautions during catheter insertion and in accordance with institutional practice standards. The ultrasound to be used will be the *Rite 8 website*, Portable device that includes real-time 2D ultrasound imaging, custom vascular access applications, procedure documentation, vessel measurement tools, and electronic connectivity.

All the material to be used will be prepared in advance and before the start of the insertion procedure, a *check list* previously established.

First, the cephalic vein of the arm will be identified, preferably under ultrasound guidance. When selecting the target vein, the insertion nurse will verify the depth of the vein, the diameter of the vein in the transverse axis of the ultrasound, counting the length and width with the application of a tourniquet, thus observing the estimated filling of the vessel lumen with the catheter provided, which should not be greater than 45%. After vein selection, the most suitable insertion site will be determined, the skin will be prepared with 2% alcoholic

chlorhexidine, and a topical anesthetic (2% lidocaine without vasoconstrictor) will be administered to the puncture site. Subsequently, the selected vein will be punctured with the tip of the Midline catheter needle, and confirmation of cannulation will be performed by US. After this confirmation, a guidewire will be advanced in the main branch of the vein and finally the wing of the introducer will be advanced into the vein and the position of the catheter tip will be confirmed by ultrasound. The tip of the catheter should not extend beyond the axillary area, and in some cases may be shorter, distal to the axilla. The percentage of the catheter lodged inside the vein will be checked and the catheter will be considered functional after observation of reflux during aspiration, followed by the administration of a flushing of 5 ml of 0.9% saline, without resistance and without infiltration. At the end of the procedure, the catheter should be stabilized with aseptic technique, coupled to a simple extender with a valved device as a distal part. The cover must be sterile with a semi-permeable transparent membrane.

### 3.5.2 Control Group

Or Control Group will be represented by hospitalized adult clinical patients who present the definition of difficult venous access (DIVA) *Difficult Intravenous Access*, characterized by the occurrence of two or more failed attempts at peripheral venous access using traditional technique, with no visible and palpable veins or patient with declared or documented history of difficult venous access and medical indication of continuous or intermittent intravenous therapy for more than 05 days and maximum 30 days of treatment. These patients will receive the insertion of a long peripheral venous catheter *Introcan Safety Deep Access* 18G (6.4 cm), 20G (6.4 cm), 22G (6.4 cm) guided by ultrasound, already recommended and instituted in the HCPA. The procedure of insertion of the long peripheral venous catheter will follow the same premises as the intervention group. The insertion will be performed by the Nurses of the Vascular Access Program of HCPA – PICC Adult Team, all with more than five years of experience in ultrasound-guided venipuncture, with previous theoretical-practical training for catheter insertion and maintenance. The insertions will be at the bedside, with adherence to standard sterile barrier precautions during catheter insertion and in accordance with institutional practice standards. The ultrasound to be used will be the *Rite 8 website*, Portable device that includes real-time 2D ultrasound imaging, custom vascular access applications, procedure documentation, vessel measurement tools, and electronic connectivity.

All the material to be used will be prepared in advance and before the start of the insertion procedure, a *check list* previously established.

First, the cephalic vein of the arm will be identified, preferably under ultrasound guidance. When selecting the target vein, the insertion nurse will verify the depth of the vein, the diameter of the vein in the transverse axis of the ultrasound, counting the length and width with the application of a tourniquet, thus observing the estimated filling of the vessel lumen with the catheter provided, which should not be greater than 45%. After vein selection, the most suitable insertion site will be determined, the skin will be prepared with 2% alcoholic chlorhexidine, and a topical anesthetic (2% lidocaine without vasoconstrictor) will be administered to the puncture site. Subsequently, the vein will be punctured with the needle tip of the long peripheral venous catheter, and the confirmation of cannulation and the percentage of the catheter lodged inside the vein will be performed with the aid of US. The tip of the catheter should always be located in the veins of the arm. The catheter will be considered functional after observation of reflux during aspiration, followed by the administration of a flushing of 5 ml of 0.9% saline, without resistance and without infiltration. At the end of the

procedure, the catheter should be stabilized with aseptic technique, coupled to a simple extender with a valved device as a distal part. The cover must be sterile with a semi-permeable transparent membrane.

### **3.6 Study outcomes and variables**

#### **3.6.1 Primary and secondary outcomes**

In this study, the primary outcome will be the duration of the cardiovascular access due to the reduction of events such as infiltration, phlebitis, occlusion, accidental removal, catheter-associated bloodstream infection and deep vein thrombosis, during the time of use of the midline catheter *compared to the use of the long peripheral intravenous catheter*.

How Secondary outcomes will be considered the reduction of events how infiltration, phlebitis, occlusion, accidental withdrawal, catheter-associated bloodstream infection, and deep vein thrombosis, first-time puncture success and economic analysis.

#### **3.6.2 Variables**

**Infiltration/extravasation** healthy Types of vascular trauma, arising from an injury to the layers of the vein and subsequent perforation, resulting in the infiltration of non-vesicant solutions or drugs into the tissues near the insertion of the venous catheter. When the solutions or drugs have vesicant characteristics, the infiltration is called extravasation. The detection of infiltration is based on clinical signs, most often edema, and may be associated with skin pallor, pain, decreased temperature and/or tenderness at the site. Infiltration may also trigger circulatory impairment and tissue necrosis in the most severe cases.

**Phlebitis** refers to an inflammation of the intimal layer of the vein, as a response to tissue injury due to several factors associated with the insertion and use of peripheral venous access devices, in addition to medications administered to it. It can be identified by signs and symptoms such as: pain, tenderness, erythema, edema, purulence or palpable venous cord. The evaluation should be regular and the patient should be instructed to report signs of pain or tenderness related to venous access. Phlebitis can be classified as mechanical, chemical, and bacterial, with a grade of 1 to 5 according to the *Visual Infusion Phlebitis* Scale.

**Occlusion** can be defined as partial or total, with partial occlusion being characterized by the ability to infuse a fluid without resistance and the absence of blood return. Total occlusion occurs when there is an inability to infuse or aspirate fluids through the catheter. Occlusion will be considered present when it is documented in the patient's medical record or when the use of thrombolysis with administration of alteplase 1mg/mL in the obstructed catheter is indicated.

**Accidental removal of the catheter** will be considered to be any premature removal of the catheter without presenting a complication as a cause.

*Catheter-Associated Bloodstream Infection (CABSI)* is used by the *Infusion Nurse Society* to refer to bloodstream infections originating from peripheral intravenous catheters and/or central vascular access devices. According to the *Centers for Disease Control and Prevention/National Healthcare Safety Network* criteria, catheter-associated bloodstream infection is defined as present when a patient has had a positive blood culture confirmed with a catheter in place for 48 hours or more, with no other source of infection identified, or if the catheter tip culture was positive in the setting of clinical suspicion of catheter infection, or if there is documentation of bacteremia or sepsis. In Brazil, the equivalent of catheter-associated bloodstream infection is called Central Line-Related Primary Bloodstream Infection, and is a notifiable healthcare-related infection. In this study, in which we will be using two types of peripheral intravenous catheters, we will use the term recommended by the *Infusion Nurse Society*.

**Deep vein thrombosis** It is a clinical condition that occurs when a blood clot forms in a deep vein, such as the axillary, brachial and subclavian veins, and these events will be investigated in the presence of clinical suspicion (pain and/or edema in the arm) and confirmed as deep vein thrombosis through an imaging test.

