Long and midline *peripheral catheters* are also indicated for infusion of peripherally compatible solutions, i.e., pH 5-9, drugs with osmolarities <600 mOsm/L, any drug or solution not associated with potential endothelial damage, history of difficult venous access, obesity, vasculopathic and/or hypovolemic diseases. In addition to the indications, these devices should be inserted by trained nurses under ultrasound guidance for cannulation of deeper veins, making the insertion technique more accurate, more successful and with less risk of complications.

Regarding the proposed therapy time and catheter permanence, international guidelines indicate the use of these catheters for peripherally compatible treatments of five to 14 days, with a permanence time of no more than 30 days. In a study with 255 patients, Bahl et al,

(2019) demonstrated that the long peripheral venous catheter had a mean length of stay of five and a half days. In a systematic review with data from 18,972 *midline* catheters, the mean length of stay was 16.3 days. In a recent retrospective cohort study in which the length of stay of long catheters was compared with midline catheters, *involving 184 patients with acute cardiovascular disease, the mean length of stay of the catheters was 14.0 days (IQR: 7.0-25.0), and the midline catheter reached 54 days of stay*.

The benefit of using a longer catheter is that it allows at least two-thirds of the catheter to reside in the vein, making it less likely to cause chemical phlebitis and infiltration. Even if the indications for the use of these devices are met, adverse events and complications may occur during their use, such as catheter-associated bloodstream infection (ACSC), venous thrombosis, occlusion, phlebitis, infiltration, and accidental removal.

In a multicenter cohort study including 5,105 *midline* and 5,758 *peripherally inserted central catheter (PICC)*, ACSC rates of 0.4% and 1.6% (midline and PICC) and occlusion rates of 2.1% and 7.0% (midline and PICC) were observed, concluding a lower risk of complications for patients using midline. Also with reference to *the midline*, the systematic review by Tripathi et al, 2021, showed that 64% of the studies did not report any catheter-related infection, with a venous thrombosis rate of 4.1%, occlusion rate of 3.8%, phlebitis 3.4%, and infiltration of 1.9%.

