### **2.2 Specific objectives**

- Analyze the indicators of good practice:

- a) Time of permanence of the venous access device free of complications: (infiltration, phlebitis, occlusion, accidental removal, catheter-associated bloodstream infection and deep vein thrombosis);
  - b) Rates of bloodstream infections associated with the type of catheter used;
  - c) Occurrence of deep vein thrombosis associated with the type of catheter;
  - d) Success rate in the first puncture attempt related to the type of catheter;
- Perform the economic analysis of the incorporation of the technology – midline catheter:
- a) Comparison of the cost of the two technologies used, type of catheter;
  - b) Costs of treatment of isolated or combined complications and catheter replacements resulting from associated infections;
  - c) Cost of avoided complications;

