### **3. METHOD**

#### **3.1 Design**

This is a randomized, parallel, open-label, controlled, single-center clinical trial, blinded to statistical analyses. In clinical trials, the investigator applies an intervention and observes its effects on outcomes. The main advantage of a clinical trial over an observational study is its ability to demonstrate causality. This study will be registered on the Platform *Clinical Trials* and will strictly follow the guidelines of the *Consolidated Standards of Reporting Trials* (CONSORT).

The economic evaluation will be based on micro-costing where all cost components are defined at the most detailed level from individual patient treatment data, such as from the medical record review. The unit of analysis in micro-costing is the individual service.

Considering the perspective of the public health system, the method seeks to assess costs as accurately as possible, including the direct and indirect costs of patient care. The time horizon considered will be 30 days. Bottom-up micro-costing will be carried out, as this is considered the gold standard for economic evaluations in health, considering that the collection of individual data enables a higher level of precision in the estimation of costs.

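### Two of the three routes to a catheter-associated bloodstream infection need no positive blood culture, so the outcome does not match the stated bloodstream-infection rate, and the daily form cannot show which route was used

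*Protocol*

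**What the plan says.** Protocol section 3.6.2 introduces the term as bloodstream infection that originates from the catheter. It then gives three criteria joined by *or*:

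1. a "positive blood culture confirmed with a catheter in place for 48 hours or more, with no other source of infection identified";
2. "or if the catheter tip culture was positive in the setting of clinical suspicion of catheter infection";
3. "or if there is documentation of bacteremia or sepsis".

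The outcome is used in four places:

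- Section 3.6.1 makes it a component of the primary outcome, among "infiltration, phlebitis, occlusion, accidental removal, catheter-associated bloodstream infection and deep vein thrombosis, during the time of use of the midline catheter", and lists it again as a secondary outcome.
- Section 2.2 sets the objective "Rates of bloodstream infections associated with the type of catheter used".
- Section 2.2 also asks for the cost of catheter replacements that follow infection.
- Section 3.10 costs the resolution of these infections in the decision-tree model.

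Section 3.1 describes the trial as "randomized, parallel, open-label, controlled, single-center clinical trial, blinded to statistical analyses". Under section 3.7, outcome data come from on-site visits, the medical record and observation of routine care. The daily monitoring form (Appendix D) has one tick-box for catheter-related bloodstream infection and no field for a blood-culture or tip-culture result.

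**The concern.** The dwell and other-source conditions sit inside the first criterion only. Under the second, a patient with negative blood cultures, or none drawn, is recorded as having a bloodstream infection if the tip grows an organism and someone suspected the catheter. Under the third, sepsis written in the chart is enough, with no stated culture result and no need to exclude a source elsewhere.

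The label and the criteria therefore describe different things. A rate reported under the section 2.2 objective could mix confirmed catheter bloodstream infection, colonised or locally infected catheters, and sepsis from another focus. The same mixture would enter the infection costs. Because the form does not record the criterion met, the mixture could not be separated afterwards without returning to the charts.

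The neighbouring component is held to a firmer standard: section 3.6.2 starts deep vein thrombosis from clinical suspicion but requires imaging to confirm it.

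**Working it through.** The protocol states no figure for this point. The check sets the criteria side by side and then asks how many infections the trial can expect.

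**What each criterion requires, as written in section 3.6.2**

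| Criterion | Positive blood culture | Dwell of 48 h or more | No other source |
|---|---|---|---|
| Blood culture | yes | yes | yes |
| Tip culture with suspicion | no | no | no |
| Documented bacteremia or sepsis | not stated | no | no |

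Documented bacteremia would usually rest on a blood culture; documented sepsis need not.

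**Arm size (section 3.4).** Inputs: difference 5 days, SD 7 days, power 90%, significance level 5% (taken as two-sided, which the protocol does not state).

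- n per arm = 2 × (1.960 + 1.282)² × 7² / 5² ≈ 41.2, rounded up to 42, or 84 in total. This reproduces the protocol's figure.
- Adding 20%: 42 × 1.20 = 50.4, rounded up to 51 per arm, or 102 in total, as stated.

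**Expected infections.** The Introduction cites rates of 0.4% for midlines and 1.6% for peripherally inserted central catheters. The second is used only as an upper reference, since that device is not studied here.

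- At 0.4%: 51 × 0.004 = 0.20 per arm and 102 × 0.004 = 0.41 overall. The chance of at least one in the trial is 1 − 0.996^102 = 0.34.
- At 1.6%: 51 × 0.016 = 0.82 per arm and 102 × 0.016 = 1.63 overall. The chance of at least one is 1 − 0.984^102 = 0.81.

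The observed count is thus likely to be zero, one or two in the whole trial. One event under the second or third criterion could be the entire infection result of an arm.

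**Effect on the primary outcome.** A tip is cultured after the catheter is out, and follow-up stops at removal (sections 3.7 and 3.8). Sending the tip therefore cannot alter the removal date. Section 3.6.2 also defines accidental removal as early removal not caused by a complication. Read literally, that can take in a catheter pulled on suspicion with no tip sent or a negative tip, giving a primary event on the same date. If that reading is not adopted, the removal would presumably be censored on that date instead, and the protocol does not say which applies.

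**The case against.** The strongest reply is that the protocol adopts one published definition and applies it to both arms. The definition and the 0.4% midline rate carry the same reference, so on the face of the document the tip-culture criterion may already be inside that 0.4%. A stricter definition gives up comparability, and with so few expected infections neither definition supports a comparison between arms. This largely stands as a limit on size. It does not repair the mismatch between the criteria and an outcome reported as a bloodstream-infection rate and costed as such.

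A reader might infer more: that colonised catheters become primary events according to whether an unblinded clinician sends the tip, and that such cases would dominate the infection result. The documents do not support this.

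- The second criterion also requires clinical suspicion, so colonisation alone does not count.
- The removal date is the same either way, and the removal may already be a primary event under another component.
- One case is 1/51 = 2.0 percentage points, about five times 0.4%, but that is true of any single event, including a culture-proven one. It shows how coarse an arm of 51 is.
- Assumed tip-only rates of 2%, 5% or 10% would add 51 × 0.02 = 1.0, 51 × 0.05 = 2.6 or 51 × 0.10 = 5.1 events per arm. Those rates are 5 to 25 times the cited total rate and have no basis in the protocol.

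Unequal culturing between a new device and the routine one is possible in an open-label trial, but nothing here shows it. Blood cultures are also ordered by unblinded staff, so a stricter definition does not remove that dependence.

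**Conclusion.** The point holds as a mismatch between an outcome and its definition. As written, two of the three criteria can record events that are not blood-culture-confirmed infections attributed to the catheter, and the study form would not reveal it.

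The infection-rate objective and the infection costs are affected. The size there cannot be stated, because the protocol gives no frequency for tip culture, colonisation or chart-documented sepsis. With about 0.2 expected infections per arm at the cited midline rate, any single misclassified event matters to that outcome.

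The effect on the primary dwell-time outcome should be small. This rests on the removal date being unchanged and on early removal for suspicion counting under another component, which the protocol allows but does not state. The sample size is unaffected.

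**What to change.** In section 3.6.2, count a case as catheter-associated bloodstream infection only with a positive blood culture, the study catheter in place for 48 hours or more, and no other source, whichever of the three criteria brought it to notice. In effect the first criterion becomes the main definition. In addition:

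- On the daily form, record which criterion was met, with fields for blood-culture and tip-culture results.
- Report tip-only positives, and chart-documented sepsis without a qualifying culture, separately from the infection rate and its costs. The cited cohort's broader definition can be kept as a sensitivity analysis for comparability.
- State that a catheter removed early for suspected infection remains a primary event on its removal date, whether or not a tip was sent. Without this, excluding tip-only cases would open a new ambiguity in the primary outcome.

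This takes a few sentences and a few form fields, and changes how outcomes are classified, not how patients are treated. If data collection has begun, infections already ticked would need to be reclassified from the charts. The downside is fewer infection events and a main definition narrower than the cited cohort's. The change reduces, but does not remove, dependence on tests ordered by staff who know the allocation.

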### **3.3 Inclusion and exclusion criteria**

a) Inclusion: Patients aged 18 years or older, after 24 hours of admission to the inpatient unit, indication of continuous or intermittent intravenous therapy during hospitalization for more than five days and who have a definition of difficult intravenous access (DIVA ), characterized by the occurrence of two or more failed attempts at peripheral venous access using the traditional technique, with no visible and palpable veins or a patient with a declared or documented history of difficult venous access.

b) Exclusion: patients requiring continuous or intermittent intravenous therapy during hospitalization for more than five days, with the presence of stage IIIB chronic renal failure with ECD <45, due to the potential need for venous arteriosus fistula in the upper limb; patients who are in COVID-19 care beds, due to the need for specific attire and time spent; who are suspected of having sepsis according to institutional protocol, who have a critical or unstable clinical condition defined by the criteria for the care of complications for adult patients at the HCPA: Airway: respiratory dysfunction requiring intubation; Respiration: respiratory rate less than 8 and greater than 35 respiratory movements per minute and/or oxygen saturation less than 90%; Circulation: heart rate less than 40 or greater than 140 beats per minute, systolic blood pressure less than 80 mmHg, systolic blood pressure between 80 and 90 mmHg, and worsening of the clinical picture; State of consciousness: decreased Glasgow Coma Scale greater than 02 points, prolonged (greater than 5 minutes) or repeated seizure; Suspicion of sepsis or a patient with cognitive impairment (as described in the patient's medical record based on medical evaluation) at the time of selection; difficulties in understanding the Informed Consent Form (ICF) (APPENDIX A) and without a family member or guardian to consent to entry into the study;

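### The third alternative in the bloodstream-infection definition has no source or timing condition, so infections unrelated to the catheter are classed as catheter-associated

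*Protocol*

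**What the plan says.** Section 3.6.2 of the protocol first explains the term: it is used "to refer to bloodstream infections originating from peripheral intravenous catheters and/or central vascular access devices". It then states when the infection counts as present, in three alternatives:

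1. "positive blood culture confirmed with a catheter in place for 48 hours or more, with no other source of infection identified"
2. "or if the catheter tip culture was positive in the setting of clinical suspicion of catheter infection"
3. "or if there is documentation of bacteremia or sepsis"

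The event is used in several places. It is part of the primary outcome in section 3.6.1, whose list ends "accidental removal, catheter-associated bloodstream infection and deep vein thrombosis, during the time of use of the midline catheter". It is a secondary outcome in the same section. It is specific objective (b) in section 2.2: "Rates of bloodstream infections associated with the type of catheter used". It is also one of the costed complications in section 3.10.

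On entry, section 3.3 excludes patients "suspected of having sepsis according to institutional protocol" and mentions suspicion of sepsis a second time. It does not name known bacteraemia.

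**The concern.** The dwell-time and source conditions belong to the first alternative only. The third is joined by a further or-if and asks for nothing beyond a record of bacteraemia or sepsis. A bacteraemia that the first alternative rejects because another source is known is therefore accepted by the third. Read literally, the third makes the care taken in the first pointless.

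The population makes this realistic. These are inpatients who need intravenous therapy for more than five and up to 30 days, and some may be receiving it for an infection. Section 3.7 draws data partly from the medical record, where a criterion based on documentation is easily met.

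At stake is whether the infection rate and infection costs describe the catheters or the patients' other infections. True catheter infections are likely to be few in a trial of 102, so a handful of unrelated events could dominate that component.

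**Working it through.** **The three alternatives side by side (section 3.6.2)**

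| Alternative | Culture required | At least 48 h dwell | Tie to the catheter |
|---|---|---|---|
| 1 | Blood | Yes | No other source |
| 2 | Catheter tip | Not stated | Suspected catheter infection |
| 3 | None | Not stated | None stated |

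**Applying the rule to three hypothetical patients**

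- Positive blood culture on day 4 with pneumonia as the known source: alternative 1 says no, alternative 3 says yes.
- Sepsis from another focus recorded 24 hours after insertion: alternative 1 says no on both timing and source, alternative 3 says yes.
- Bacteraemia already under treatment at entry, with no suspected sepsis: not excluded by section 3.3, and alternative 3 says yes.

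**Looking for a repair elsewhere**

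- Section 3.8 fixes when follow-up ends. It does not say where an infection must come from.
- The daily form (Appendix D) has one tick-box for catheter-related bloodstream infection and no criteria.
- The baseline form (Appendix C) lists sepsis as an undated risk factor. Nothing says that such an entry is not an event.

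**The plan's own figure**

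Inputs from section 3.4: difference 5 days, SD 7 days, power 90%, significance level 5% (taken as two-sided).

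n per arm = 2 × (1.960 + 1.282)² × 7² / 5² = 2 × 10.51 × 1.96 = 41.2, rounded up to 42. The total is 84, as stated. Adding 20%: 42 × 1.2 = 50.4, rounded up to 51 per arm, or 102, as stated. The point about the definition does not depend on this figure; only the arm size of 51 is used next.

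**Size for the infection component**

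The documents give no rate of bacteraemia or sepsis from other sources. Let q be the assumed proportion of patients with such a record, and suppose that every case is recorded as the rule reads. Expected misclassified events per arm = 51 × q.

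| q (assumed) | Per arm of 51 | Both arms, 102 |
|---|---|---|
| 1% | 0.5 | 1.0 |
| 2% | 1.0 | 2.0 |
| 5% | 2.6 | 5.1 |
| 10% | 5.1 | 10.2 |

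For scale only, the 0.4% midline rate cited in the Introduction gives 51 × 0.004 = 0.2 events per arm.

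**Direction for the primary comparison**

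Section 3.10 compares complication-free survival by Cox analysis and a log-rank test. Let h1 and h0 be the true hazards in the midline and control arms, with h1 < h0, and let c be an equal background hazard of misclassified events. The observed ratio is (h1 + c)/(h0 + c). It stays below 1, and it exceeds h1/h0 by c(h0 − h1)/[h0(h0 + c)], which is positive. The ratio moves towards 1 and does not cross it.

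**What dilution would cost, if it occurred**

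Using the section 3.4 model, power = Φ(d / (7 × √(2/42)) − 1.960), where d is the remaining difference.

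| Assumed shrinkage of the 5 days | d | Power |
|---|---|---|
| 0% | 5.00 | 0.905 |
| 5% | 4.75 | 0.875 |
| 10% | 4.50 | 0.838 |
| 20% | 4.00 | 0.745 |

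The shrinkage values are assumptions. The documents offer no way to get from q to a shrinkage, so this table shows sensitivity and is not an estimate.

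**The case against.** **Attribution is implied.** The term itself says catheter-associated, its explanation in section 3.6.2 speaks of catheter origin, and the daily form's box says catheter-related. A sensible researcher might not tick that box for pneumonia. This shows what the authors probably meant. It does not change the operative rule, and two researchers could apply it differently.

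**The sentence may be a loose translation.** The third alternative could be read as a second setting for a positive tip culture. The repeated or-if argues against that, and a definition open to both readings still needs correcting.

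**Suspected sepsis is excluded at entry.** This stands for sepsis present at selection. It does not cover known bacteraemia, or sepsis from another focus that arises later.

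**The primary outcome is partly protected.** The Introduction frames the hypothesis around complications that cause the access to be taken out or replaced, so an unrelated infection that leaves the catheter in place would not count. This stands and limits the point considerably. Sections 2.2 and 3.6.1 do not repeat that limit, so the protection is incomplete.

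**Two stronger readings are tempting and are not supported.**

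- A reader might infer that false events count against the device that stays in longer. The Cox and log-rank methods in section 3.10 account for time at risk, so an equal background hazard dilutes the contrast and does not penalise longer dwell. Crude counts could behave differently, but the documents do not allow that to be sized.
- A reader might infer, by setting an assumed 2% to 10% against the cited 0.4%, that more than 80% of recorded infections would be false. That share only restates the assumption. The protocol also credits the 0.4% and the three-part definition to the same reference, a multicentre cohort of midlines and PICCs, so 0.4% cannot be taken as a true rate free of the third alternative.

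**Conclusion.** Wrong as written. The third alternative, followed literally, produces a classification that the first is designed to prevent. This is a rule that the protocol states itself, not a detail left to an analysis plan.

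The main consequence is for the infection rate, the secondary infection outcome and the infection costs. On an assumed 1% to 10% of patients with unrelated bacteraemia or sepsis, all recorded as the rule reads, the misclassification is about 0.5 to 5 events per arm; the true figure cannot be had from the protocol. For the primary outcome the documents support dilution only, of unknown and probably small size, on the assumption that the background hazard is equal in the two arms.

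**What to change.** Reword the third alternative only, in one of two ways:

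- bacteraemia or sepsis documented as attributed to the study catheter; or
- bacteraemia or sepsis with onset after insertion, the catheter in place for 48 hours or more, and no other source identified.

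Leave the second alternative unchanged, because a positive tip culture with suspected catheter infection already ties the event to the device. Add an item to the baseline form for bacteraemia present at randomisation, and state that it is a baseline characteristic and not an event.

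The cost is one sentence in section 3.6.2 and one tick-box. No extra tests, visits or patients are needed.
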